#### Primary outcome measure

Changes in pain intensity, measured on the 100 mm visual analogue scale (VAS) [32], at 9 weeks after beginning treatment.

#### Secondary outcome measures

▪ Changes in pain intensity, measured on the 100 mm VAS, at 6 months after beginning treatment.

▪ Changes in the McGill Pain Questionnaire (MPQ), at the end of treatment and after 6 months. The MPQ pain evaluation index consists of 64 pain descriptors divided into 19 subclasses. Within each subclass, the descriptors are classified by intensity.

▪ Satisfaction on the improvement perceived by the patient (PPI) [33], scored by the patient on a 7-point Likert scale as follows: 1 = extremely satisfied; 2 = very satisfied; 3 = moderately satisfied; 4 = no strong feelings either way; 5 = somewhat unsatisfied; 6 = very unsatisfied; 7 = extremely unsatisfied.

▪ Changes in health-related quality of life, according to the Spanish version of the 12-item Short Form health survey, Version 2, at the end of treatment and after 6 months. This questionnaire is of a generic type, derived from SF-36, which has been validated for use in Spain [34], and which enables the quantification of quality of life in 8 dimensions (physical function, physical role, pain, general health, vitality, social function, emotional role, mental health) and expresses two summary components (physical and mental).

▪ Changes in the results of the Lattinen test and in the consumption of analgesics and NSAIDs (whether or not prescribed by the GP), at the time of randomization, after each treatment session, at the end of treatment and after 6 months.

#### Control of blinding and assessment of treatment credibility

The patients will be asked to answer the following questions:

• Expectations and confidence in the treatment (ECT), evaluated after the third auricular pressure session, and scored on the original scale of Borkovec and Nau [35] with four items, scored on a numerical scale of 0 to 10 (0: totally disagree; 10: totally agree): (1) Are you confident that this treatment will relieve the pain you feel?; (2) Does the treatment seem to be a logical one?; (3) Would you recommend this treatment to a friend or relative suffering the same complaint?; (4) Do you believe this treatment would be a possible option for dealing with other problems?

• Verification of the patient's blinding (VB) [36]. After the final treatment session, the patient will be asked: "What treatment do you think you were given?" The possible answers are: 1 = true auricular pressure; 2 = sham auricular pressure; 3 = Not sure.

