We have designed this randomised controlled multicentre study to investigate the effectiveness and safety of sensory stimulation via auricular implants in patients with UCR, treated by healthcare professionals (15 doctors and nurses) at 10 healthcare clinics in the Sevilla-Sur Healthcare District (within the Andalusian Public Health System). The primary specific goal is to assess effectiveness in terms of the lessened pain intensity, measured on a visual analogue scale (VAS), experienced by patients with UCR, at 9 weeks after beginning treatment. As secondary specific goals, we intend to: a) evaluate the effectiveness in terms of lessened pain intensity, measured on the VAS, at 6 months after beginning treatment; b) evaluate the effectiveness in terms of improvement recorded on the Spanish version of the McGill Pain Questionnaire (MPQ-SV), at 9 weeks and at 6 months after beginning treatment; c) evaluate the effectiveness in terms of patient-perceived improvement (PPI) at the end of the treatment; d) evaluate the impact on time lost off work due to sickness; e) evaluate the credibility of the technique and patients' expectations, as well as its relation to the results; f) evaluate the effectiveness in terms of reduced consumption of analgesic and anti-inflammatory medication; g) evaluate the effectiveness in terms of improved health-related quality of life (SF-12); h) compare the effectiveness of the technique with regard to the healthcare professionals' degree of training and practice; i) compare the characteristics of the Lattinen test and the MPQ-SV; j) analyze the cost-effectiveness of treatment with auricular pressure for patients with UCR.

This study is funded by the *Instituto de Salud Carlos III*, *Fondo de Investigaciones Sanitarias *(File No. PI0790058) and by the Health Ministry of the Andalusian Regional Government (File No. 00462007).

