### Treatment

The 15 healthcare professionals who will participate in the study (doctors and nurses) have taken a training course in auricular pressure techniques for the treatment of UCR, with a total of 15 hours' theory and 15 hours' practical content. Of these 15 professionals, 5 had also received specific training in acupuncture and related techniques, with an average of 320 hours theoretical training and over 100 hours' clinical practice with these techniques. All the patients will be allowed to use symptomatic medication for pain relief in case of need.

The patients in both groups will be called 8 times for treatment (once a week) for the auricular implants to be inserted.

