### Results measures

Each patient will fill in a self-response questionnaire before beginning the treatment (T0), at one week after ending treatment (T1) and after six months (T2). This questionnaire will include one-dimensional data (100 mm visual analogue scale) and multidimensional data (McGill Pain Questionnaire, Spanish version [30]) on rachialgia, medication currently being taken and health-related quality of life (SF-12), together with information on days off work due to rachialgia. Additionally, before beginning treatment, the patients will be asked to fill in a form on sociodemographic questions. Any adverse effects of the study techniques, and any use of rescue medication by the patient will also be recorded. During the initial evaluation, an anamnesis will be obtained on the characteristics of the rachialgia, and note will be taken of the duration of the pain. In each treatment session, the therapist will record the five pain-related variables that constitute the Lattinen test (LT), which is widely used in pain treatment clinics in Spain [31]. These variables are: pain intensity, pain frequency, consumption of analgesics, level of activity, and nocturnal hours' sleep. Each item is scored on a Likert scale from 0 to 4; thus, the sum of the five variables may range from 0 to 20 points, with higher scores reflecting greater pain severity. In addition, the auricular points selected for each patient will be recorded (Table 1).

**Table 1 T1:** Data collection schedule. Measurement times and variables used in the study.

Visit No.	T0	Weekly treatment								T1	T2
Week No.	0	1	2	3	4	5	6	7	8	9	24
Data provided by the patient											
Pain intensity (VAS 100 mm)	X									X	X
Multidimensional pain evaluation (MPQ-SV)	X									X	X
Quality of life (SF-12)	X									X	X
Analgesics and antiinflammatory drugs prescribed	X									X	X
Sociodemographic variables	X										
Credibility and expectations				X							
Improvement perceived by the patient										X	
Assessment of blinding effectiveness										X	
Data provided by the therapist											
Multidimensional pain evaluation (LT)	X	X	X	X	X	X	X	X	X	X	X
Auricular points used		X	X	X	X	X	X	X	X	X	
Adverse events		X	X	X	X	X	X	X	X	X	
Economic evaluation											
Direct and indirect costs: healthcare professionals and patients	X									X	X

VAS 100 mm: Visual analogue scale (0–100 mm); MPQ-SV: McGill Pain Questionnaire, Spanish version; LT: Lattinen test

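### Expectation is measured only after the third of eight sessions, so its planned relation to the results may partly reflect relief already felt

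*Protocol article*

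**What the plan says.** Secondary goal (e), in the Background of the protocol article, is to "evaluate the credibility of the technique and patients' expectations, as well as its relation to the results". The instrument is a four-item scale, each item scored 0 to 10, described under Control of blinding and assessment of treatment credibility. It is "evaluated after the third auricular pressure session". Its first item asks "Are you confident that this treatment will relieve the pain you feel".

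Table 1 (Results measures) agrees with the text. The row "Credibility and expectations" has one mark, in the week-3 column, and none at T0. The Treatment section sets eight weekly sessions in both groups.

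The primary outcome is "Changes in pain intensity, measured on the 100 mm visual analogue scale (VAS) [32], at 9 weeks after beginning treatment". VAS pain is recorded at T0, T1 (week 9) and T2 only. The therapist records the Lattinen test, which includes pain intensity, at T0 and at every session. The Statistical analysis section describes no analysis of the expectation score.

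**The concern.** Goal (e) concerns what patients expect of the treatment and how that relates to what they obtain. A rating given after three sessions can draw on experience as well as prior belief. A patient whose pain has already eased has reason to report confidence that it will be relieved, and a disappointed patient has reason not to. The outcome is change from T0, so it contains the same early weeks. Score and outcome can thus share a cause, early response, and be associated even if prior expectation does nothing.

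At stake is the interpretation of one secondary goal. A positive association could not be separated into patients who expected relief and then obtained it, and patients who obtained relief early and then reported confidence. An analysis plan written later cannot recover a pre-treatment score that was never collected.

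**Working it through.** The protocol gives no figure for the expectation–outcome relation, so there is none to reproduce. The check shows how large an association could arise when prior expectation has no effect.

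**Inputs from the protocol article (Sample size)**
- Mean VAS reductions of 32.3 and 19.8 mm, a difference of 12.5 mm; SD 31.9 mm; 140 per group after losses, so 280 completers.
- The sample size holds up: 2 × (1.960 + 1.282)² × 31.9² / 12.5² ≈ 137 per group, against 140 stated (two-sided 5%, 90% power). Also 140 / (1 − 0.30) = 200 per group, or 400 in all, as stated.

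**Assumptions (not in the documents)**
- r1, the correlation of change by week 3 with change by week 9: 0.3, 0.5, 0.7.
- r2, the correlation of change by week 3 with the week-3 score: 0, 0.2, 0.3, 0.5.

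**Model, standardised within arm**
- Week-9 change = r1 × early change + √(1 − r1²) × independent noise.
- Week-3 score = r2 × early change + √(1 − r2²) × prior expectation.
- Prior expectation is independent of early change and of outcome, so its true effect is zero.

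Early change is then the only link between score and outcome:
- spurious correlation = r1 × r2
- spurious slope = r1 × r2 × 31.9 mm per SD of score

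The last column comes from 2,000 simulated trials per setting, regressing week-9 change on arm and week-3 score, with a 5% two-sided test of the score.

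| r1 | r2 | r1 × r2 | Slope, mm per SD | Significant at 5% |
|---|---|---|---|---|
| 0.3 | 0 | 0 | 0 | 4.4% |
| 0.3 | 0.2 | 0.06 | 1.9 | 16% |
| 0.3 | 0.3 | 0.09 | 2.9 | 33% |
| 0.3 | 0.5 | 0.15 | 4.8 | 70% |
| 0.5 | 0 | 0 | 0 | 5.3% |
| 0.5 | 0.2 | 0.10 | 3.2 | 38% |
| 0.5 | 0.3 | 0.15 | 4.8 | 71% |
| 0.5 | 0.5 | 0.25 | 8.0 | 99% |
| 0.7 | 0 | 0 | 0 | 4.5% |
| 0.7 | 0.2 | 0.14 | 4.5 | 64% |
| 0.7 | 0.3 | 0.21 | 6.7 | 94% |
| 0.7 | 0.5 | 0.35 | 11.2 | 100% |

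Monte Carlo standard error at a 5% rate is √(0.05 × 0.95 / 2000) ≈ 0.5 percentage points, so the r2 = 0 rows are nominal.

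**With expectation taken before session 1.** Testing prior expectation in the same simulated trials gives 4.4% to 5.9% significant across all settings, which is nominal.

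**With the week-3 score adjusted for early change.** The rate is 4.2% to 6.1%. This rests on early change measured without error and on expectation having no effect, so it cannot show what the adjustment would cost if expectation did act.

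**The case against.** **The scale is there for credibility.** It sits under blinding and credibility, not among the outcomes, and credibility is reasonably asked once patients have experienced the treatment. This stands, and is why the week-3 measure should remain. It does not supply a measure of prior expectation, which goal (e) needs.

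**No causal claim is written down.** A reader might infer that the trial will report the association as an effect of expectation. The documents do not say so, and an association between week-3 confidence and outcome is a legitimate descriptive result. The analysis model may properly be left to a document not shown here. What this document does fix is the absence of any pre-treatment score.

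**The size is assumed.** This also stands. If early response does not move the score, the problem vanishes. At r1 = r2 = 0.3 the spurious correlation of 0.09 is below the roughly 0.117 needed for 5% significance with 280 completers. Contamination is possible and, given the wording of the first item, plausible; it is not established.

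**Credibility and blinding.** A reader might go further and infer that early efficacy would make credibility look unequal between arms and so mislead about blinding. The documents do not carry that as a fault. Asking after some exposure is acceptable for credibility, blinding has its own question after the final session, and a T0 item would leave the week-3 comparison between arms unchanged.

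**Existing data might suffice.** The Lattinen change from T0 to week 3 is available, so one could adjust for it. But if expectation works by producing early relief, that change is a mediator and adjustment would remove part of a true effect. The scale is also coarse, with items scored 0 to 4, and is recorded by a therapist who is told the allocation by phone and fax (Randomization and treatment allocation).

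**Conclusion.** The point holds as a modest design weakness confined to secondary goal (e). The timing is stated consistently in text and table: expectation is measured once, after three of eight sessions, with nothing at T0. An association with week-9 VAS change could therefore arise without any effect of prior expectation.

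Under assumed correlations of 0 to 0.5 (early response with score) and 0.3 to 0.7 (early response with outcome), the spurious correlation is 0 to about 0.35, or 0 to about 11 mm of VAS change per SD of score. These figures rest wholly on the assumed ranges; they are not estimates for this trial.

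The randomised primary comparison and the sample size are untouched. This is a cheap improvement, not a defect that threatens the trial.

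**What to change.** - Add the expectation items to the T0 questionnaire, after the treatment has been explained and before the allocation call. At a minimum add item 1, confidence that the treatment will relieve the pain. Items 3 and 4 (recommending it, and using it for other problems) presuppose some experience and are less needed at T0.
- Name the T0 score as the predictor for the relation to results in goal (e).
- Keep the week-3 measure for credibility, and report its relation to outcome as descriptive only.
- Treat adjustment of the week-3 score for Lattinen change from T0 to week 3 as at most a sensitivity analysis, with the mediation and measurement limits stated.

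The cost is one to four extra 0–10 items on a questionnaire patients already complete. For patients already enrolled when the change is made, the T0 score cannot be recovered, and only the descriptive week-3 relation is available.

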#### Sociodemographic variables

The following data on sociodemographic variables will be recorded: age, race, sex, marital status, educational level, financial level and occupational activity.

### Data collection and analysis

#### Data collection

The data will be compiled in a general questionnaire addressing each of the study variables, both in the self-administered formats and in those applied by direct observation. These data will be sent to the study coordinator at the end of the follow-up evaluation of each patient.

#### Recording study data and information on adverse effects

A record will be kept of any side effects experienced, and of possible adverse events arising from either the experimental or the pharmacological treatment.

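### Table 1 schedules no adverse-event entry after week 9, although the text promises, with no end date, to record drug-related events, and drug use is recorded at week 24

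*Protocol article*

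**What the plan says.** Four parts of the protocol article bear on this.

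- **Scope of the record.** The section on recording study data and adverse effects says: "A record will be kept of any side effects experienced, and of possible adverse events arising from either the experimental or the pharmacological treatment". No end date is given. The description of the placebo arm under Treatment adds a logbook for reactions, with details and date of occurrence, also without an end date. The text of Results measures mentions adverse effects of the study techniques only.
- **Timing of the record.** Table 1 is the only place that says when adverse events are collected. Its columns are "Week No. 0 1 2 3 4 5 6 7 8 9 24", and the row reads "Adverse events X X X X X X X X X". The nine marks fall on weeks 1 to 9. T0 and T2 are blank.
- **Drug use.** The Table 1 row "Analgesics and antiinflammatory drugs prescribed" is marked at weeks 0, 9 and 24. The Lattinen test, which contains an analgesic-consumption item, is marked at every visit including T2. Secondary outcome measures lists Lattinen scores and analgesic/NSAID consumption "at the time of randomization, after each treatment session, at the end of treatment and after 6 months". The Background makes lower consumption a secondary goal: "f) evaluate the effectiveness in terms of reduced consumption of analgesic and anti-inflammatory medication".
- **Treatment period.** Implants are applied at eight weekly sessions and each stays in place for a week. Symptomatic medication is allowed in both arms (Treatment, Discussion).

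**The concern.** The text extends the adverse-event record to the drugs patients take, and those drugs do not stop when the implants do. A week-9 end suits the implants but not the medication. A site that follows Table 1 will ask about analgesics and NSAIDs at week 24, but nothing in the schedule prompts it to ask whether they, or the earlier implants, caused any problem since week 9.

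At stake is how complete the safety record is over follow-up. The trial presents itself as a study of effectiveness and safety and hopes to see less drug use. If consumption differs between arms at 6 months, a reader will naturally ask whether drug-related events differ too. After week 9 the answer would rest on whatever was reported unprompted.

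**Working it through.** The documents give no figure for this gap, so there is none to reproduce. The check sets the rows of Table 1 against its week row.

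**Inputs (protocol article, Table 1)**

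| Row | Weeks marked |
|---|---|
| Visit columns | 0, 1–8, 9 (T1), 24 (T2) |
| Adverse events | 1–9 |
| Prescribed analgesics/anti-inflammatories | 0, 9, 24 |
| Lattinen test | 0, 1–8, 9, 24 |

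**Step 1: length of the gap.** Last visit minus last scheduled adverse-event entry: 24 − 9 = 15 weeks. As a share of follow-up: 15/24 = 62.5%. If 6 months is read as 26 weeks instead of the table's 24, the gap is 26 − 9 = 17 weeks (17/26 = 65.4%).

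**Step 2: what the gap consists of.** No visit is scheduled between weeks 9 and 24, so the omission is a single unmarked cell at T2. The therapist supplies data at T2, because the Lattinen row in the therapist's block is marked there. No new visit is needed to fill the cell.

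**Step 3: is the implant exposure covered?** Eight weekly sessions run over weeks 1 to 8. The last implant stays in place for one week, which takes exposure to about week 9. The scheduled entries at weeks 1 to 9 span it. Only implant effects that appear late fall outside.

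**Step 4: is the drug exposure covered?** Medication is permitted as needed, and its consumption is an outcome at 6 months. Drug exposure can therefore continue through weeks 9 to 24, where no adverse-event entry is scheduled.

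**Step 5: effect of the fix.** An entry at T2 that asks back to T1 covers weeks 9 to 24 retrospectively and leaves 0 weeks without a scheduled entry. The sample size of 140 per group is derived from VAS change alone and does not move.

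**The case against.** A blank cell in a summary table is not a prohibition. The logbook and the adverse-effects section are open-ended, and each patient's data go to the coordinator only after the follow-up evaluation, so late entries are not shut out. The safety aim in the Background concerns the auricular implants, whose exposure weeks 1 to 9 cover. The drugs are permitted in both arms and are not randomised. Confining scheduled entries to the intervention period plus about a week is a recognisable choice for seeds held by sticking plaster, and a full protocol might give more detail.

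Most of this stands, and it limits the point. A reader might infer from Table 1 that weeks 9 to 24 will have no safety data at all. The documents do not support that: they show only that no entry is scheduled, and spontaneous reports may still be logged. A reader might also infer that a planned comparison of drug-related events between arms is lost. No such comparison is planned: the goal on medication is framed as effectiveness through lower consumption, and the analysis section deals chiefly with the primary outcome.

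The objection does not remove the mismatch. The article itself fixes both the scope, which includes drug-related events without limit of time, and a schedule that stops before the drug follow-up does. This is a disagreement between two statements, not detail left to a fuller document. Unprompted reporting is also weaker than a question put to every patient at a visit.

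**Conclusion.** The point holds as a minor inconsistency. Table 1 has no adverse-event entry for the last 15 of 24 weeks, while the text commits to recording events from the experimental or the pharmacological treatment with no end date, and drug use is recorded at T2. The gap concerns late events and drug-related events in weeks 9 to 24. Implant safety during treatment, the primary outcome, the sample size and the randomisation are not affected.

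The 15 weeks rest on reading T2 as week 24, as the table does, and on sessions being held on schedule. It is tempting to turn 62.5% of follow-up time into a number of missed events. The documents do not allow that: they give no event rate, nothing shows that the rate is constant over time, the plan itself allows for 30% drop-out, and the logbook may capture some events.

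**What to change.** Reconcile Table 1 with the section on recording adverse effects:

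1. Mark the adverse-event row at T2.
2. At that visit, ask every patient about events since T1. Record the date and suspected cause of each, keeping the implants apart from analgesics/NSAIDs.
3. Report incidence by arm separately for weeks 0–9 and weeks 9–24, and give the number of patients seen at T2 as the denominator for the second period.

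The cost is one extra mark in Table 1 and one question at a visit that already takes place. The drawback is the quality of the second-period data: recall of about 15 weeks, and weak attribution to drugs because no drug use is scheduled to be recorded between weeks 9 and 24. The report should state this and should not pool the two periods as if they were collected in the same way.

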#### Statistical analysis

A comparison will be made of the baseline variables for each of the groups, to test the homogeneity obtained from the random allocation to groups, in terms of differences of the means and of proportions. The magnitude of the difference in the possible imbalance produced by the random allocation between the two groups will be quantified in terms of ratios of the means and of proportions (using that of the placebo group as a reference level), and the final adjustment will be made by secondary analyses with multiple linear regression models.

In the unadjusted analysis, significance tests will be performed for comparison among k samples (parametric or otherwise, depending on whether or not the distribution of the outcome variables is asymmetric, and on the homogeneity of their variances), taking that of the placebo group as a reference level, and using comparison tests for differences of the means in the primary outcome measure (pain intensity on the 100 mm VAS), both for the inter-group comparisons (for independent samples) and for comparisons between the initial and final levels in each group (in this case, using tests for non-independent or paired samples).

Linear regression models will be constructed for the primary outcome measure, adjusted by the baseline level and using ITT analysis. The group variables will be included, taking that of the placebo group as a reference level, together with the results recorded by the medical professionals, and the sociodemographic data (age and sex), and the baseline levels for the variables related to the severity of the process (pain intensity and frequency). Adjustments will be made for possible confounders, using criteria of statistical significance and of confusion. The detection of possible interactions with the treatment group variable will be evaluated using criteria of statistical significance for the corresponding interaction terms. The level of statistical significance will be set at α < 0.05. The model will be reconstructed, removing the observations with Cook's distances exceeding the 90^th ^percentile of the distribution, in order to test the consistency of the results.

An economic analysis will also be carried out, from the standpoint of the interests of the Andalusian Public Health System.

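### Baseline homogeneity tests and ratios of means are a poor basis for the secondary adjustment to which the plan links them

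*Protocol article*

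**What the plan says.** The first paragraph of the Statistical analysis section sets out three linked steps.

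- Baseline variables are compared "to test the homogeneity obtained from the random allocation to groups", by way of differences in means and proportions.
- The size of a possible imbalance is "quantified in terms of ratios of the means and of proportions", with placebo as the reference.
- The same sentence ends by stating that "the final adjustment will be made by secondary analyses with multiple linear regression models".

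The third paragraph describes the regression model for VAS pain. It is adjusted for the baseline level and analysed by intention to treat, and it names age, sex, and baseline pain intensity and frequency among its terms. A separate rule then follows: "Adjustments will be made for possible confounders, using criteria of statistical significance and of confusion". The section works at one level throughout: "The level of statistical significance will be set at α < 0.05".

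The Randomization and treatment allocation section describes a central, computer-generated 1:1 sequence in blocks of 6, stratified by therapist and kept concealed.

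**The concern.** If allocation was properly random and concealed, the hypothesis that the two arms come from the same population is true. A significant baseline difference is then a chance event. It carries no information on whether the variable predicts VAS pain, and that is what matters for adjustment. A prognostic variable can equally be out of balance by a relevant amount without reaching significance.

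The ratio has a different weakness. Its distance from 1 reflects the imbalance in SD units multiplied by the coefficient of variation (CV, the SD divided by the mean). Variables with a large SD relative to their mean will show striking ratios by chance, while those with a small one will show ratios near 1 even when the imbalance is the same.

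The sentence runs from this assessment to the final adjustment and mentions no prognostic criterion. It therefore leaves room for the observed imbalance to shape the secondary adjusted estimates. That is an avoidable data-driven step.

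**Working it through.** **The plan's own figures.** The plan gives no number for baseline balance. Its sample size supplies the inputs below and can be reproduced. The difference is 32.3 − 19.8 = 12.5 mm, the SD is 31.9 mm, two-sided α is 0.05 and power is 90%. Then n = 2 × (1.960 + 1.282)² × 31.9² / 12.5² ≈ 137 per group (138 with the t distribution), against 140 stated. Allowing for 30% dropout, 280 / 0.70 = 400, as stated, or 200 per arm at baseline.

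**Step 1: chance of at least one significant baseline difference.** For k independent tests at 0.05 under correct randomisation this is 1 − 0.95^k. The Sociodemographic variables section lists seven variables; the larger values of k are assumptions, since the plan does not say how many variables are compared.

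| k | Chance of at least one |
|---|---|
| 7 | 30% |
| 10 | 40% |
| 15 | 54% |
| 20 | 64% |
| 28 | 76% |

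Positive correlation between the variables would lower these figures.

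**Step 2: how the ratio behaves.** With an imbalance of d SD units, the ratio of means is 1 + d × CV. By chance alone its standard error is about CV × √(2/n), which is 0.10 × CV at n = 200 per arm. The 95% chance range is exp(±1.96 × SE). The CVs are assumptions.

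| CV | Ratio when d = 0.2 | 95% chance range of the ratio |
|---|---|---|
| 0.2 | 1.04 | 0.96 to 1.04 |
| 0.5 | 1.10 | 0.91 to 1.10 |
| 1 | 1.20 | 0.82 to 1.22 |
| 2 | 1.40 | 0.68 to 1.48 |

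A departure from 1 of more than 10% arises by chance in about 5% of trials at CV 0.5 and about 62% at CV 2.

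A ratio of proportions has a related weakness, because it depends on which category is counted. For example, 10% against 5% gives 2.0, while the complement, 90% against 95%, gives 0.95.

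**Step 3: what a non-significant result can hide.** The largest imbalance that stays non-significant is about 1.96 × √(2/n), which is 0.196 SD at 200 per arm. If the variable has correlation ρ with VAS change, the unadjusted difference shifts by 0.196 × ρ × 31.9 mm. For ρ = 0.3 this is 1.9 mm and for ρ = 0.7 it is 4.4 mm, or 15% to 35% of the planned 12.5 mm. The range for ρ is an assumption. This shift concerns the unadjusted comparison; it does not carry through for a variable that is already in the model.

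**The case against.** The case on the other side is substantial, and much of it stands.

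- **No p-value is named.** The baseline sentence speaks of testing homogeneity by differences of means and proportions. Significance tests are first mentioned in the next paragraph, for the outcome. So significance testing at baseline is an inference. It is still the natural reading in a section that works at α 0.05, and the remark on ratios does not depend on it.
- **The ratio is not the only measure.** Differences are also planned, and a ratio of proportions is an ordinary summary. Choosing standardised differences instead is largely a matter of presentation.
- **The link to covariate choice is not spelled out.** The paragraph does not say that imbalanced variables are the ones adjusted for. The later rule for confounders, if it means confounding in the usual sense, takes account of association with the outcome and would tend to screen out irrelevant variables. What remains is that one sentence joins the measure of imbalance to the final adjustment, and the plan does not close that route.
- **A balance check can have some use.** Blocks are of fixed size 6 within therapist, and the professional who enrols patients learns each allocation. Later allocations in a block could be guessed if the block size became known. A significant difference is therefore not a chance finding with complete certainty. That would be a reason to look into the allocation process; it gives no guidance on which covariates to adjust for.

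A reader might also infer that the plan will declare randomisation to have failed, or that the main VAS result will be distorted. The document supports neither. It attributes possible imbalance to the random allocation itself and sets no cut-off. It also puts baseline level, age, sex, and baseline pain intensity and frequency in the VAS model regardless of the balance table.

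**Conclusion.** The point holds in a narrow form, as a minor improvement that costs almost nothing. Homogeneity tests between randomised arms and ratios of means are not sound grounds for choosing adjustment variables, and the plan ties them to the final secondary adjustment. The effect is confined to the statement on balance and to any secondary adjusted estimate led by observed imbalance. The sample size, the primary outcome and the named baseline terms of the VAS model are untouched.

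The firmest figure is the 30% chance of at least one significant result among the seven sociodemographic variables. It assumes one test per variable at 0.05, independence and intact concealment. The longer lists of variables, the CVs and the correlations with VAS change are assumptions, used only to show direction and range.

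**What to change.** Change the first paragraph of the Statistical analysis section in three ways.

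1. Delete the test of homogeneity. State that baseline data are described by arm, with no p-values.
2. If a magnitude of imbalance is wanted, report standardised differences (the difference divided by the pooled SD) in place of ratios.
3. Separate the description of balance from the adjusted analyses. State that these use the baseline covariates already named in the section (baseline level, age, sex, and baseline pain intensity and frequency), whatever imbalance is observed. Bring the later sentence on possible confounders into line, so that imbalance does not re-enter by that route.

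The cost is a few sentences and fewer tests to run. No data item, patient visit or sample size changes.
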